##### Perceived food environment

Perceived Nutrition Environment Measures Survey (NEMS-P) by Green and Glanz [66] will be used to assess the parents’ perceived food environment. The NEMS-P core components that measured community (seven items), consumer nutrition environment (24 items), and home food environment (seven items) will be examined. Composite scores will be calculated for each domain.

Community nutrition environments assess the store and restaurant accessibility, including mode of travel to the store, distance travelled to store/restaurant, as well as store motivation (importance of store proximity to home and other places where time is spent) and restaurant motivation (importance of convenience).

Consumer nutrition environments can be further categorized into store consumer and restaurant consumer nutrition environment. Store consumer nutrition environments include 17 items on store availability of healthy food choices, store motivation, price of fruits and vegetables, placement or promotion of unhealthy/healthy items, and nutrition information. Subjects will be asked to indicate their level of agreement on the statements using a 5-point scale ranging from “strongly disagree” (1) through “strongly agree” (5). Store motivation such as the importance of selection, quality, and price of food is assessed using a 4-point scale ranging from “not at all important” (1) through “very important” (4). Pricing for fruits and vegetables is assessed using response choices of very expensive (1) to very inexpensive (4). For the restaurant consumer nutrition environment, a total of seven items will be assessed on the availability of healthy options, promotions, and the cost of healthy options at restaurants using a 5-point scale ranging from “strongly disagree” (1) through “strongly agree” (5).

The home food environment includes items on the availability and accessibility of healthy and unhealthy food in the home. Subjects will be asked to indicate the availability of fruits/vegetables, healthy food, and unhealthy food based on the given list. Besides, the accessibility of healthy and unhealthy food will be assessed using a 4-point scale of “never or rarely” (1) to “almost always” (4).

##### Perceived built environment

Physical Activity Neighbourhood Environmental Survey (PANES) by Sallis et al. [67] will be used to assess the parents’ perceived environmental support for physical activity. A total of 17 questions will be asked in measuring the attributes of neighbourhood built and social environments hypothesized or known to be related to physical activity using a 4-point Likert scale ranging from “strongly disagree” (1) through “strongly agree” (4). The items can be categorized as residential density (item 1), land use mix (items 2 and 17), transit access (item 3), pedestrian infrastructure (items 4 and 13), bicycling infrastructure (items 5 and 14), recreational facilities (item 6), street connectivity (item 12), crime safety (items 7 and item 16), traffic safety (items 8 and 15), pedestrian safety (item 9), aesthetic (item 10). The mean total score will be calculated and the higher the score, the higher the perceived neighbourhood environment support for physical activity.

### Data management and analysis

Data analysis will be performed using IBM SPSS 25.0 (SPSS Inc., Chicago, IL, USA). A test of normality will be performed using a skewness value (between − 2 and + 2) for the continuous variables. The univariate analysis will be used to report descriptive data including mean score, median, and standard deviation for continuous variables and percentage and frequencies for categorical variables. Independent-samples *t*-test and One-way ANOVA will be used to compare differences between groups for continuous variables and chi-square analysis will be conducted to examine associations for categorical variables. Correlation test will be used to see if correlation exist between variables. A paired-samples *t*-test will be conducted to determine the statistical differences between the two monsoon seasons. Logistic regression will be performed separately for seasons to determine the relationship between nutritional status and selected variables (Food security, lifestyle factors and neighbourhood environment factors). The Generalized Linear Mixed Model will be used to determine the seasonal effects on food security, lifestyle factors, neighbourhood environmental factors, and its effects on nutritional status. The significance level for all analyses is set at *p* < 0.05.

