### Study setting and sampling method

This study followed a multistage stratified random sampling design **(**Fig. 1**)**. First, a complete list of the People’s Housing Programme (*Perumahan Awam, PA or Program Perumahan Rakyat, PPR*) (*n* = 53), located in Kuala Lumpur is obtained from the Kuala Lumpur City Town Hall (*Dewan Bandaraya Kuala Lumpur, DBKL*) and further stratified into four zone areas based on the zone office management by DBKL. Subsequently, three flats from each zone area will be randomly selected (*n* = 12). A convenience sampling method will be applied for the recruitment of the subjects whereby the residential president of PA/PPR shared e-flyers through social media platforms with the residents for the recruitment of the adolescents via the parents. In addition, adolescents will be also approached by door-to-door recruitment methods at all the residential blocks. All adolescents from all ethnicities within the selected flats are invited to participate in the study. The purpose and procedures of the study will be explained to the adolescents and their parents/guardians. A detailed information sheet will be provided for a better understanding of the study. Parents/guardians will be requested to sign a written informed consent to allow their child’s participation, and assent will be obtained from adolescents to indicate their willingness to participate before the commencement of the study. Data collection will be conducted by enumerators who have been trained, monitored, and supervised throughout the study. Each adolescents will be given a unique identification number to ensure anonymity. The flow diagram of the study is depicted in Fig. 2.

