#### Spatial food and built environment

Spatial food and built environment are defined using a buffer zone area of defined geographic distance from the low-cost flats. QGIS 3.4 Madeira will be used to generate walking-distance circular buffers for a distance of 1000 m on-street network away from residential flats. These are the common buffer sizes applied in active research transport as this is the distance that can be covered by a 10–15-minute walk [42]. The exact address of each selected flats is required, which will be converted into geographic coordinates. The spatial data of all food and built establishments within the residential neighbourhood environment are geocoded to obtain latitude and longitude, where on-site data collection will be performed using a Qmini A7 High-precision (country that produce it) GIS handheld device. Types of food establishments included are supermarkets (e.g., AEON, GIANT, TESCO, large local wet markets, etc.), fast-food restaurants (e.g., KFC, Pizza Hut, McDonald’s, Texas Chicken, etc.), restaurants, convenience stores (e.g., 7-eleven, KK mart, Shell Mart, etc.), street food and specialty food stores (e.g., bakeries, fruit and vegetables, gourmet, meat and fish markets). Built establishments for physical activity included parks and public recreational facilities (e.g., soccer fields, basketball courts, community centers, pools, and playgrounds). Besides, the location of bus stops and the station will also be collected. The assumption is made that no substantial changes in the distribution and number of this food and built establishments throughout the study.

Using the geocoded data, the following spatial neighbourhood food and built environment indicators will be created: (1) density of food and built establishments within 1000 m network buffer zones; and (2) proximity to food and built establishments (closest distance, via the street network, from PA/PPR to each type of food and built establishment). The density and proximity to the food and the built establishments will be determined in QGIS software using the Buffer, Mapping, and Count Point analysis tools.

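### The between-adolescent tests and season-specific logistic regressions ignore clustering by flat, which makes p-values too small for the spatial exposures measured once per flat

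*Protocol article*

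**What the plan says.** **Sampling.** Under Study setting and sampling method the article says "This study followed a multistage stratified random sampling design". The 53 public housing schemes are divided into four zones, and "three flats from each zone area will be randomly selected", giving 12. A flat here is a housing scheme, not a dwelling. Within flats recruitment is by convenience: "All adolescents from all ethnicities within the selected flats are invited to participate in the study". No limit of one adolescent per household is stated.

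**Exposure level.** Under Spatial food and built environment, "The exact address of each selected flats is required, which will be converted into geographic coordinates". Density is counted in a 1000 m network buffer around that location. Proximity is the "closest distance, via the street network, from PA/PPR to each type of food and built establishment". Both are properties of the flat. The same section assumes that outlets and facilities do not change materially during the study. Food security is a household score reported by the parent (Household food security status).

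**Analysis.** Data management and analysis names independent-samples t-tests, one-way ANOVA and, for categorical data, "chi-square analysis will be conducted to examine associations for categorical variables". It adds correlations, a paired t-test between seasons, and a logistic regression of nutritional status in each season on food security, lifestyle and neighbourhood factors. A generalized linear mixed model is assigned to the seasonal effects. "The significance level for all analyses is set at" p < 0.05. No cluster term, robust variance or design effect is stated for the between-adolescent tests or the logistic regressions.

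**The concern.** Adolescents in one flat share a location and probably much else, so their outcomes may be positively correlated. An independent-observations test counts each adolescent as separate evidence on an exposure that all residents of the flat share. With any positive intracluster correlation (ICC), the standard error for such an exposure is then too small and chance differences between flats are declared significant too often.

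At stake are the associations between the spatial food and built environment and nutritional status. The Discussion presents the combined spatial and perceived measurement as a strength and expects the findings to inform policy.

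**Working it through.** **Inputs**
- 12 flats, three in each of four zones (Study setting and sampling method).
- Prevalence 15.8%, precision 0.05, 95% confidence, N = 204 raised to 256 (Sample size calculation).
- Alpha 0.05 (Data management and analysis). Sidedness is not stated; two-sided is assumed.
- ICC: not given. 0.01 to 0.10 is assumed, with flats of equal size.

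**Step 1: reproduce the plan's sample size.** n = 1.96² × 0.158 × 0.842 / 0.05² = 204.4 (stated 204). 204.4 × 1.25 = 255.5, rounded up to 256 (stated 256). Both figures reproduce under simple random sampling, so no design effect was included.

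**Step 2: flat-level exposure.** m = 256/12 = 21.33 per flat. DEFF = 1 + (m − 1) × ICC. The naive standard error is 1/√DEFF of the correct one. The true type I error is 2 × [1 − Φ(1.96/√DEFF)].

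Example, ICC 0.05: DEFF = 1 + 20.33 × 0.05 = 2.02; 1/√2.02 = 0.70; type I error 16.8%.

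The formula was checked by simulation with 20,000 replicates per setting, 12 flats × 21 = 252 adolescents and a beta-binomial outcome at 15.8%. A naive chi-square test compared 6 with 6 flats, and a naive logistic score test used a continuous flat-level exposure.

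| Assumed ICC | DEFF | Naive SE / correct SE | Type I error, formula | Simulated: chi-square / logistic |
|---|---|---|---|---|
| 0 | 1.00 | 1.00 | 5.0% | 4.8% / 5.2% |
| 0.01 | 1.20 | 0.91 | 7.4% | 7.0% / 6.9% |
| 0.02 | 1.41 | 0.84 | 9.8% | 9.6% / 9.2% |
| 0.05 | 2.02 | 0.70 | 16.8% | 16.4% / 16.5% |
| 0.10 | 3.03 | 0.57 | 26.0% | 25.9% / 25.8% |

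If only 204 adolescents are available (17 per flat), the formula gives 6.9%, 8.8%, 14.4% and 22.4% for ICC 0.01 to 0.10.

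**Step 3: household-level exposure (food security).** For sibling pairs, DEFF = 1 + (share of adolescents with a sibling in the sample) × (household ICC). The documents give neither figure. A share of 25% with ICC 0.2 gives DEFF 1.05 and 5.6% error. A share of 100% with ICC 0.5 gives DEFF 1.5 and about 11%.

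**Step 4: exposures that vary within flats.** DEFF = 1 + (m − 1) × ICC(exposure) × ICC(outcome), with m = 17. For exposure ICC 0.05 to 0.10 and outcome ICC 0.02 to 0.10, type I error is 5.2% to 6.9%. It rises to between 6.1% and 10.7% only if the exposure is itself strongly clustered (ICC 0.3).

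**Step 5: prevalence precision.** Half-width = 1.96 × √(0.158 × 0.842 × DEFF / N). At N = 204 the planned 0.05 becomes 0.054, 0.057, 0.067 and 0.081 for ICC 0.01 to 0.10. At N = 256 it is 0.049, 0.053, 0.064 and 0.078.

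**Step 6: degrees of freedom.** A flat-level slope from 12 flats has 12 − 2 = 10 df (critical value 2.23). With four zones fitted it has 12 − 4 − 1 = 7 df (critical value 2.36). The naive tests use about 1.96.

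**The case against.** The strongest reply has four parts.

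- **The mixed model.** It is the analysis named for the third objective and can carry flat and household effects. An article may leave its random effects to the full plan. This stands, and the unstated random effects are not counted as a fault here. It does not cover the t-tests, ANOVA, chi-square tests and season-specific logistic regressions, which are named separately and take the neighbourhood factors.
- **Seasonal change is the main aim.** The paired t-test removes stable flat and household effects, so only clustering of the change scores remains. This stands, and the point does not reach that contrast.
- **Most exposures vary within flats.** For these the inflation is small unless the exposure is strongly clustered. This stands, so the point should not be read as invalidating every planned test.
- **The ICC is assumed.** This stands for the size. The direction holds for any positive ICC.

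A reader might also draw three stronger conclusions that the documents do not support.

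- *The study has 12 observations rather than 256.* At ICC 0.01 to 0.05 the effective sample is about 213 to 127. The number of flats limits degrees of freedom; it does not reduce the data to 12 points.
- *The spatial indicators are planned as seasonal outcomes.* Nowhere are they listed as such. Table 1 repeats only the perceived surveys, the second objective omits the neighbourhood, and the spatial section treats outlets as constant.
- *All reported prevalence intervals will be too narrow.* The analysis section specifies no interval method. Only the sample size formula implies simple random sampling.

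**Conclusion.** The point holds, mainly for flat-level spatial exposures in the between-adolescent tests and season-specific logistic regressions. There a nominal 5% test has a true error of about 7% at ICC 0.01 and about 26% at ICC 0.10. These figures assume 12 equal flats, about 21 adolescents each, and an ICC that the documents do not give. The effect on household food security is moderate and depends on sibling enrolment, which is possible under the open invitation but of unknown frequency. If blocks within a scheme were geocoded separately there could be slightly more than 12 values, but the text ties the measures to each selected flat.

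This should be fixed, but it does not undermine the main seasonal comparison.

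**What to change.** - In the season-specific regressions and between-group comparisons, account for flat with a random intercept, or use cluster-robust or GEE inference with a small-sample correction for 12 clusters. Add household where siblings can be linked and the model is estimable. With about 40 obese adolescents expected (0.158 × 256 = 40.4), it may not be.
- State the same flat effect in the mixed model.
- Test flat-level spatial indicators against a t reference with about 10 df, or about 7 if the four zones are fitted, or in an analysis of flat-level summaries.
- Report prevalence intervals that allow for clustering by flat. Strictly design-based intervals are not available, because recruitment within flats is by convenience.
- Enter the spatial indicators only as time-invariant flat-level covariates, in line with the article's own constancy assumption.

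**Cost.** This is a change of analysis wording. The status section says the data had not been processed for analysis at submission. Flat membership must be known to assign the spatial values. The article mentions only a unique number per adolescent, so household linkage needs confirming. Intervals will be wider, and power for spatial exposures will be low with 12 flats.

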## Background

Although many actions and efforts had been made, malnutrition in all forms, including overnutrition (overweight and obese) and undernutrition (underweight, wasting, stunting and micronutrients deficiencies), as well as diet-related non-communicable diseases (diabetes, cardiovascular diseases), continues to be alarming public health issues all over the world including both developed and developing countries [1]. According to Country Nutrition Report by Global Nutrition Report, Malaysia has been recently classified as one of the Asian countries that is currently experiencing a triple burden of malnutrition, where overweight coexists with stunting and anaemia [2]. This urges the need for urgent action to identify and address the root causes of public health issues.

As defined by World Health Organization (WHO)_,_ defines adolescents are young people aged between 10 and 19 years [3]. It is well recognized that adolescence is the vital period in the life span that experiences major anatomical, physiological, and social changes as a form of transition. During this transition from childhood to adulthood period, children begin to explore and develop their identities as a result of complex interactions with their families, communities, and culture that accompany all domains of autonomy development [4]. This dynamic period of human growth makes adolescents nutritionally vulnerable as the pubertal transition during this period is accompanied by a growth spurt where extra macronutrients and micronutrients are required [5, 6]. The burden of malnutrition can harm adolescents in multiple ways, including impaired growth, osteopenia, anaemia, retard sexual maturation, and these consequences have been shown to be associated with the early onset of chronic diseases in adulthood [7].

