## Methods

### Study aim

The main aim of the study is to examine the seasonal variation in food security, lifestyle factors, neighbourhood environmental factors, and nutritional status of the urban poor adolescents in Kuala Lumpur, Malaysia. To achieve the aim, the specific research objectives to be investigated in the study are as follows:To determine the food security, lifestyle factors, neighbourhood environmental factors, and nutritional status of the urban poor adolescents in Kuala Lumpur, Malaysia.To determine the seasonal differences in food security, lifestyle factors, and nutritional status among urban poor adolescents in Kuala Lumpur, Malaysia.To determine the effects of season on food security, lifestyle factors, neighbourhood environment, and its effects on the nutritional status of the urban poor adolescents in Kuala Lumpur, Malaysia.

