### Study design

This is a cohort study that stemmed from two cross-sectional studies that will be carried out during the onset of the Northeast Monsoon season and will be followed up during the Southwest Monsoon season to capture a different season. Recruitment of the subjects will begin upon obtaining ethical clearance from the Institutional Ethics Committee of UCSI University [Reference code.: IEC-2021-FAS-03)] and permission to conduct the study from Kuala Lumpur City Town Hall (DBKL) [Reference code: DBKL/JPKKB/SPZ/29–3 Jld 13 (48)].

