**Adolescent’s Questionnaire and Assessment**		
Pubertal Development Scale	*	*
2-day diet recall	*	*
Eating Behaviours Questionnaire	*	*
Physical Activity Questionnaire for Older Children	*	*
Screen time	*	*
Step counts	*	*
Changes in lifestyle-related behaviour during COVID 19 pandemic	*	
Modified Harvard step test	*	*
Body weight	*	*
Height	*	*
Waist circumference	*	*
Body fat percentage	*	*
Haemoglobin level test	*	*

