#### Adolescent’s questionnaire and assessment

##### Physical development

Pubertal Development Scale (PDS) will be used to assess the pubertal status of adolescents [43, 44]. A total of five items are assessed in PDS to rate the growth spurt, body hair growth, and skin changes using a four-point scale: “not yet started” (1), “barely started” (2), “definitely started” (3), “seems complete” (4), and “I don’t know” (0). On a similar scale, boys will be asked to rate their development of facial hair and voice change, whereas girls rated their breast development and whether they have reached menarche, present (4) and absent (1). Based on the sum of the scores, adolescents will be categorized into pre-pubertal, early pubertal, mid-pubertal, late pubertal, and post-pubertal [43, 44].

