##### Anthropometric measurements

All equipments will be calibrated before the measurements are performed. The body height of subjects will be measured using a calibrated vertical stadiometer (Seca 213 portable stadiometer, SECA GmbH & Co., KG. Hamburg, Germany), whereas weight and body fat percentage will be measured using the Bioelectrical Impedance Analyzer (OMRON HBF-375 Karada Scan Body Composition Monitor, OMRON HEALTHCARE Co., Kyota, Japan). Both height and weight measurements are recorded to the nearest 0.1 cm and 0.1 kg, respectively. The nutritional status of adolescents will be determined based on Z-scores for height-for-age (HAZ) and BMI-for-age (BAZ) of WHO growth reference 2007 for adolescents between 5 and 19 years old using WHO AnthroPlus version 1.0.3 software (WHO, Geneva, Switzerland). The classification as followed, stunting (HAZ < -2SD), normal height (HAZ > -2SD), thinness (BAZ < -2SD), normal weight (−2SD ≤ BAZ ≤ +1SD), overweight (+1SD < BAZ ≤ +2SD), and obesity (BAZ > +2SD) [59]. The body fat percentage will be classified using percentile scores for sex and age based on the findings by McCarthy et al. [60] into underfat (<2nd percentile), normal (2nd – 85th percentile), overfat (>85th – 95th percentile), and obese (>95th percentile).

Waist circumference will be measured at the midway between the lowest rib and the superior border of the iliac crest as recommended by WHO [61] using a non-elastic SECA 201 Ergonomic circumference measuring tape (DECA GmbH & Co., Hamburg, Germany) to the nearest 0.1 cm. A cut-off point of the 90th percentile of waist circumference percentile classification for Malaysian children and adolescents [62] will be used to identify abdominal obesity. For adolescents aged 17 years and above, WHO/IASO/IOTF (2000) for Asian cut-off [63] will be used instead. Abdominal obesity was defined as ≥90 cm for men and ≥ 80 cm for women. Mean average values will be used for data analysis.

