##### Anaemia status assessment

A haemoglobin level test will be performed to identify the anaemia status of each adolescent by using the HemoCue haemoglobinometer (HemoCue® Hb 201+ System, Angelholm, Sweden), point-of-care testing on capillary blood samples. Anaemia status and level of severity are determined according to the age and gender-specific haemoglobin cut-off point as defined by WHO [64]: (i) < 115 g/L for 5 to 11 years of age; (ii) < 120 g/L for 12 to 14 years of age and non-pregnant women (15 years of age and above); (iii) < 130 g/L for men (15 years of age and above).

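### One cycle in one fixed order, tested by an unadjusted paired t-test, cannot tell season apart from ageing or calendar change, and the limitations do not say so

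*Protocol article*

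**What the plan says.** All references are to the protocol article.

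- **Design.** Study design places the baseline at the "onset of the Northeast Monsoon season and will be followed up during the Southwest Monsoon season to capture a different season". Table 1 shows one baseline and one follow-up assessment. Neither season is repeated and nobody starts in the other season.
- **Objective.** The second objective in Study aim is "To determine the seasonal differences in food security, lifestyle factors, and nutritional status among urban poor adolescents".
- **Test.** In Data management and analysis, a paired-samples t-test "will be conducted to determine the statistical differences between the two monsoon seasons". No covariate is attached to it. The same section also plans a Generalized Linear Mixed Model (GLMM) for seasonal effects.
- **Ageing.** The Background notes that "the pubertal transition during this period is accompanied by a growth spurt". The Pubertal Development Scale is marked at both visits in Table 1, but no stated analysis uses it. Physical development scores the don't-know answer as 0, one below the answer for not yet started. It then says: "Based on the sum of the scores, adolescents will be categorized into pre-pubertal, early pubertal", and so on through the later stages.
- **Cut-offs.** Anaemia status assessment uses 115 g/L up to age 11, 120 g/L from 12, and for males "< 130 g/L for men (15 years of age and above". For abdominal obesity, Anthropometric measurements uses a percentile rule and then changes it: "For adolescents aged 17 years and above, WHO/IASO/IOTF (2000) for Asian cut-off".
- **Pandemic.** The Table 1 row "Changes in lifestyle-related behaviour during COVID 19 pandemic" is marked at baseline only. The Discussion accepts that pandemic effects on some study variables may have been missed. It does not mention visit order or ageing, and it lists the two time points as a strength.

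**The concern.** With one cycle in one order, the second visit always means three things at once: the Southwest Monsoon, an older adolescent, and a later date in a changing pandemic. A paired t-test on the difference estimates the sum of the three. The main aim is the seasonal effect, and the Discussion offers the results to policymakers for seasonally sensitive programmes. A change that comes from growth or from the end of restrictions could therefore be presented as a monsoon effect.

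A second, separate issue concerns anaemia as a category. The cut-off rises at set birthdays, so a participant with unchanged haemoglobin can move from not anaemic to anaemic between visits. Neither haemoglobin step can produce the opposite move.

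**Working it through.** **The plan's own figure.** n = 1.96² × 0.158 × 0.842 / 0.05² = 204.4, which the plan gives as 204; 204.4 × 1.25 = 255.5, rounded up to 256. Both reproduce. They concern baseline prevalence of obesity. No effect size or SD of change is given for the seasonal comparison, so 204 and 256 serve below only as plausible numbers of pairs.

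**Interval between visits.** Baseline ran from 1 November 2021 to 30 April 2022 (status and timeline section), and the Southwest Monsoon runs from late May to September (Background). Assuming follow-up in 2022 and taking late May as 25 May:
- shortest: 30 April to 25 May = 25 days, about 1 month
- longest: 1 November to 30 September = 333 days, about 11 months
- midpoints: 30 January to 28 July = 179 days, about 6 months

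**Can the effects be separated?** Write each outcome as intercept + season + calendar period + age at visit. Season and period are both 0 at visit 1 and 1 at visit 2 for everyone, so the design matrix has rank 3 with 4 columns. No model, the GLMM included, can split season from period. Season and age at visit alone have full rank (3 of 3), because adolescents differ in age. Using within-person information only, age separates from season only if intervals vary (rank 206 of 206 with varying intervals, 205 of 206 with a constant interval, for 204 adolescents).

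**Size of the problem for the t-test.** Let the seasonal effect be zero and the drift be d SDs of the paired change. For a two-sided 5% test, the probability of significance is approximately Φ(d√n − 1.96) + Φ(−d√n − 1.96). The values of d are assumptions.

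| d | 204 pairs | 256 pairs |
|---|---|---|
| 0 | 5% | 5% |
| 0.05 | 11% | 13% |
| 0.1 | 30% | 36% |
| 0.2 | 82% | 89% |
| 0.3 | 99% | >99% |

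For raw waist, with assumed growth of 1 cm and SD of change 3 cm, t = 1/(3/√204) = 4.8. With 0.5 cm and SD 4 to 5 cm, t = 1.8 to 1.4, not significant. The result depends on growth and SD figures that the article does not give.

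**Anaemia category.** Assume ages uniform from 10 to under 18 (8 years), half boys, and a 6-month interval.
- Passing 12: 0.5/8 = 6.25%
- Boys passing 15: half of 6.25% = 3.1%
- Total 9.4%, about 19 of 204 (1.6% at 1 month, 17% at 11 months)

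Added anaemia with unchanged haemoglobin = 6.25% × P(115 to 120) + 3.125% × P(120 to 130). Take normal distributions with assumed means of 128–130 g/L near 12 and 138–140 g/L in boys near 15, and SD 10–12:
- smallest (130, 140, SD 10): 6.25 × 0.092 + 3.125 × 0.136 = 1.0 points
- largest (128, 138, SD 12): 6.25 × 0.113 + 3.125 × 0.186 = 1.3 points

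One common mean for both groups (125 or 130 with SD 10, or 135 with SD 12) gives 1.1 to 2.1 points, so the figure is sensitive to the means chosen.

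**The case against.** - **Much is already age-referenced.** Anthropometric measurements bases nutritional status on HAZ and BAZ, and classifies body fat, and waist below 17, by percentiles. This stands. The ageing argument is confined mainly to raw waist, raw body fat percentage, haemoglobin, fitness score and possibly activity. Food security is a household score and diet quality is scored against recommendations; the article gives no growth mechanism for either. Calendar change can still reach all of them.
- **A GLMM is already planned.** This stands, and a condensed article need not list its covariates. What remains is a stated choice: the article gives the between-season difference to the paired t-test. The GLMM also cannot remove the confounding with calendar period.
- **The t-test is never assigned to binary outcomes.** Correct. A reader might infer that birthdays across cut-offs distort the paired t-test. They do not: they affect categorical status, not a t-test on continuous haemoglobin or waist.
- **The anaemia shift assumes unchanged haemoglobin.** If haemoglobin rises with age in boys, part of the shift is offset. This stands, and the figure is conditional.
- **Pandemic effects are acknowledged.** Only as possibly overlooked. The limitation that season coincides with visit order and ageing is absent. Asking the pandemic items again at follow-up would not separate season from recovery either.

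**Conclusion.** The concern holds in bounded form. Season is fully confounded with calendar period and, in the unadjusted t-test, with ageing and puberty. The article does not say so, although its main aim is the seasonal effect.

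A reader might infer that the planned test will report growth as season across all outcomes. The documents do not support that: they give neither the size nor the direction of any drift, and HAZ, BAZ and the percentile classes are age-standardised. The supported statement is that such changes cannot be told apart from season.

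If the drift in an affected measure were 0.1 to 0.2 SD of the paired change, the false-positive rate at 204 pairs would be about 30% to 82% against a nominal 5%. The separate anaemia artefact is about 1.0 to 1.3 percentage points over an assumed 6 months, given the assumed age distribution, means and SDs and unchanged haemoglobin.

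**What to change.** 1. Make the already planned GLMM the seasonal analysis in place of the paired t-test. Use a link suited to each outcome (identity for continuous, logit for binary), a random intercept per adolescent, and fixed effects for age at visit, sex and pubertal stage at visit. Date of birth and the pubertal scale are already collected.
2. Analyse haemoglobin as a continuous outcome for the seasonal comparison, and keep the age-specific anaemia classes as descriptive.
3. Score the pubertal don't-know response as missing, not 0, before the scale is used as a covariate. As coded, it moves uncertain adolescents towards a less mature class.
4. State in the limitations and conclusions that one cycle in one order shows change between two waves, and that no model can separate season from calendar period.

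**Cost.** Wording in the analysis plan and the report, with no new data. The article says that the data had not yet been processed for analysis at submission. The downsides are a more modest claim, and an age adjustment that relies on age differences between adolescents and on varying visit intervals.
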